## Abstract

*Purpose*. The SenseWear Armband (SWA) is a multisensor activity monitor that can be used in daily life to assess an individual's physical activity level (PAL). The primary goal of this study was to analyze the impact of different types of feedback on the PAL of Flemish employees. *Methods/Design*. We recruited 320 sedentary employees (age, 41.0 ± 10.7 years; BMI, 26.2 ± 4.2 kg/m^2^) to participate in the 12-month study. Participants were randomized into one of four intervention groups after being measured for 7 days and nights by means of the SWA: (1) a minimal intervention group received no feedback (MIG, *n* = 56); (2) a pedometer group was provided only information on their daily step count (PG, *n* = 57); (3) a display group received feedback on calories burned, steps taken, and minutes of physical activity by means of the SWA display (DG, *n* = 57); (4) a coaching group also received the display and had weekly meetings with a Personal Coach (CoachG, *n* = 57). We hypothesize that participants receiving feedback (SG, DG, and CoachG) will have a greater increase in physical activity outcome variables compared to participants of the minimal intervention group.

## 1. Introduction

Increasing daily physical activity (PA) is a key strategy for preventing or minimizing numerous chronic diseases [1, 2]. Daily PA consists of all occupational, domestic, and leisure-time activities. While participation in leisure-time activities has remained relatively stable over the years, technological advancements have drastically reduced occupational PA [3]. People spent more time at sedentary occupations or in work-related activities such as passive commuting (e.g., driving/riding in a motorized vehicle), which has a negative impact on total PA [4]. 

Given the benefits of regular PA and the current high prevalence of physical inactivity, people need strategies to increase their level of PA [5]. In 1996, the American College of Sports Medicine proposed PA guidelines which stated that 30 minutes of moderate-intensity exercise on most days provide some health benefits, notably, a decreased risk of chronic diseases. Moderate intensity PA is defined as activity performed at 3–6 MET and corresponds with the equivalent of walking 3-4 mph for most healthy adults. Because inactive people show measurable health benefits with only small increases in activity levels, these people should be targeted in health-promotion programs [6].

 The physical activity level (PAL) of an individual is widely used as an indirect measure of physical activity energy expenditure. It can be measured or estimated from the average of 24-hour total energy expenditure (TEE) and the basal metabolic rate (BMR) (i.e., PAL = TEE/BMR). The expression of energy requirements of adults as PALs provides a convenient way of controlling for age, sex, weight, and body composition. A meta-analysis of studies that involved a total of 411 men and women from 18 to 64 years of age with a predominantly sedentary western lifestyle showed a mean value for PAL of 1.60 (range 1.55 to 1.65) for both men and women [7]. A PAL value of 1.75 and higher includes the regular practice of PA at work or in leisure time with an intensity and duration that will reduce the risk of becoming overweight and developing a variety of noncommunicable chronic diseases.

Research has revealed an association between a person's physical activity level and his/her lifestyle. According to the 1981 FAO/WHO/UNO expert consultation, an active or moderate active lifestyle corresponds with a PAL value between 1.70 and 1.99. According to this expert panel, the daily performance of one hour (either continuous or in several bouts during the day) of moderate to vigorous exercise, such as jogging/running, cycling, aerobic dancing, or various sports activities, can raise a person's average PAL from 1.55 (corresponding to the sedentary category) to 1.75 (the moderately active category). 

Inactive subjects are often not aware of the fact that they are insufficiently active. Physical activity awareness—defined as the agreement between self-rated and actual activity level according to current guidelines—has rarely been studied as a determinant of healthy behavior change. People are only expected to consider changing their behavior when they become aware that they personally engage in too little PA and are potentially putting their health at risk [8]. One way of raising awareness of individual physical (in)activity levels compared with perceived (in)activity levels is to monitor their physical (in)activity, for instance, by using objective measures such as a pedometer or a multisensor activity monitor [9].

Several studies have promoted pedometers as effective tools to increase walking [10, 11]. The 10,000 steps/day program has been the most popular proposal [12]. Pedometers measure walking through step counts and have been proven to be both reliable and valid [13, 14]. Most of the research on pedometers has focused on their use as a measurement device for assessing PA and not as a motivational tool [15]. Recently, studies examining the effectiveness of pedometers in promoting PA have shown that PA programs consisting of a pedometer, a daily goal defined in steps, and a step diary will increase physical activity levels by 2500 steps on average, compared with a sedentary control group [16–18]. It therefore has been concluded that pedometers can motivate individuals by monitoring the step count and operate as a tracking device and goal setting tool [19].

Although pedometers are easy-to-use motivational instruments, their major drawbacks are that they cannot reflect intensity of movement and therefore result in inaccurate energy expenditure estimations [20]. By contrast, the SenseWear Pro3 Armband (SWA) (BodyMedia, Inc. Pittsburgh, PA, USA) is a multisensory device that is worn on the upper arm and receives information from a dual-axial accelerometer to measure motion and multiple sensors to measure skin temperature, heat flux, and galvanic skin response. The SWA also works with a watch-like display device that gives the user real-time feedback on calories burned, steps taken, and time spent in various intensity zones. Time spent in moderate, vigorous, and very vigorous activities corresponds with MET values greater than or equal to 3 and less than 6, greater than or equal to 6, and greater than or less than 9, respectively. Such a sophisticated accelerometer-based device has advantages over pedometers when energy-related output variables are a desired outcome. When people are given information on the energy expenditure (kilocalories) and the time spent (minutes) of physical activities above a predetermined intensity level as well as the number of steps, they will have a very detailed description of their own physical (in)activity pattern. To our knowledge, no study has so far investigated whether specific feedback on various dimensions of the physical (in)activity behavior leads to a greater increase of the individual's physical activity level compared with more basic feedback on their number of steps.

When people are being measured, they become more self-conscious about their own behavior. It is well documented that promoting PA using simple, attainable behavioral strategies such as self-monitoring, goal setting, and physical (in)activity behavior feedback is effective for interventions [21]. Self-monitoring increases awareness of energy expenditure, enhances self-efficacy, allows for individuals to monitor progress and change over time, and thus can be an effective tool for behavioral change. Goal setting has shown some promise in promoting dietary and PA behavior change among adults [22]. Cullen et al. [23] developed a four-step goal-setting process which consists of (1) recognizing a need for change, (2) establishing a goal, (3) adopting a goal-directed activity and self-monitoring it, and (4) self-rewarding goal attainment. Adding feedback and rewards to the goal-setting process can increase motivation and task performance, and ultimately this leads to behavior change. Feedback can be described as knowledge of personal status about one's selected goal and should be provided regularly to adapt or adjust to the required behavior [24]. Information from a PA monitor can help the user in attaining their exercise goals. The simple retargeting of information about the physical (in)activity behavior to the individual can have immediate impact on their exercise behavior. Paschali et al. [25] used simple accelerometers to track activity among adults with type 2 diabetes. This pilot study examined whether giving activity feedback to obese, sedentary adults with type 2 diabetes would improve their adherence to a home-based walking program. Since the authors could not significantly contribute the increase in PA to the feedback condition, they concluded that further studies with larger sample sizes and greater control of experimental conditions were needed to determine the utility of objective activity feedback.

The SenseWear display is a recent innovation which allows progress monitoring throughout the day and indicates in real time when goals have been met. This technology can help motivate people towards predetermined activity goals allowing them to have a clearer picture of their physical (in)activity pattern. Setting specific goals is an important aspect of coaching as the effectiveness of coaching revolves around the nature of the goals established by the individual and the processes by which they are achieved. Coaching is a behavioral strategy recently emerging in the literature and works as an effective strategy in achieving lifestyle change [26]. The social interactions provided by a coach may provide useful forms of modeling and social support that can enhance the initial adoption of health behaviors such as PA [27]. Understanding the factors that can motivate health-enhancing PA has considerable value given the role of this lifestyle behavior in promoting quality of life. One theoretical perspective that appears useful for understanding motivation and adherence to exercise is the self determination theory [28]. SDT particularly describes the processes through which a person acquires the motivation for initiating new health-related behaviors and maintaining them over time. The theory focuses on the degree to which people's motivation toward engagement in activities, such as PA, is more or less self-determined (autonomous) or controlled by external or internal pressures [29]. People are autonomously motivated when they engage in an activity or cease an activity for reasons that are freely chosen. In a PA context, people are autonomously motivated if they choose to initiate PA for enjoyment and/or because they think PA is important and will help them attain valued goals and/or because of personal commitment to improving their health or quality of life. Research has shown that autonomous motivation leads to greater long-term persistence, for example, maintained change toward healthier behaviors [30].

SDT proposes that humans have three basic psychological needs of autonomy, competence, and relatedness that must be satisfied in order for growth and well-being to be achieved [31]. Autonomy relates to the desire to be the regulator of one's actions, and that behavior is volitional. People perceive themselves to be competent when they feel capable of attaining health outcomes, such as meeting a PA goal. The construct of perceived competence is very similar to the self-efficacy concept [32, 33], which has been found to be one of the strongest predictors of PA in adults [34]. Relatedness refers to experiencing care and concern from important individuals and feeling connected and understood by others [35]. SDT argues that developing a sense of autonomy and competence is critical to self-regulate and sustain health-promoting behavior. Equally important is relatedness, as people are more likely to adopt behaviors promoted by those whom they trust [36].

Over the years, the number of social factors that have been found to affect people's needs and, in turn, motivation has been growing [37]. How other people behave has tremendous impact on the needs being satisfied and, in turn, on motivation being optimal or not. One of the key interpersonal dimensions studied is autonomy support which can be defined as the active support of the person's capacity to be self-initiating and autonomous [38]. Autonomous supportive environments can be established by acknowledging the feelings and perspectives of the individual, by providing sufficient information, by minimizing pressure and control, and by offering freedom of choice [38]. 

SDT has been utilized with a variety of health behaviors. Silva et al. [39] implemented an SDT-based intervention for weight management, facilitating exercise adherence by enhancing the more autonomous forms of behavioral regulation. Patrick and Canevello [40] used a computerized intervention based on SDT to better understand the psychological mechanisms in regard to PA frequency, intensity, and duration in sedentary young adults. These studies highlight the positive influence that autonomy support can have on facilitating health behavior change as well as associated physical and psychological health benefits [41]. 

Well-designed randomized controlled trials (RCTs) could help in understanding what types of interventions promote change in a particular behavior. Research shows that individually tailored interventions are more likely to be read, saved, remembered, and discussed [42], and that goal setting in combination with self-monitoring is more successful [27, 43]. We hypothesize that the use of the feedback generated by a SenseWear display or a pedometer will increase awareness of employees own physical (in)activity pattern and feelings of competence and results in an increased PAL in comparison with a minimal intervention group.

For motivational purposes, a simple, low-cost step counter may suffice, and these are more feasible from a cost-efficiency perspective than sophisticated accelerometer-based devices [44]. Because the SWA display gives continuous feedback about people's (in)activity behavior and specific activity goals can be set, research is needed to compare the individual's adherence with a healthy lifestyle when feedback is given by a pedometer or a multisensor activity monitor. This study has the additional purpose to compare the effectiveness of feedback given by a pedometer and a multisensor device. We hypothesize that activity monitors that display specific feedback on several parameters of an individual's activity pattern, namely, steps, calories, and minutes spent on PA will motivate people to increase their activity level more than monitors who only track step counts.

The coaching is based on the SDT of Deci and Ryan. This theory states that the extent that the environment allows one to experience feelings of competence, autonomy, and relatedness will influence the person's motivation toward a given task. The behavior of a coach has a strong impact on people's needs being satisfied and, in turn, on their motivation being optimal or not. It can be speculated that if the relation with a coach leads to relatedness satisfaction, the message and values transmitted by the coach may be more readily internalized by the participant. Furthermore, to the extent that the coach also supports the client's autonomy, such internalization will be autonomous in nature, thereby leading to positive and long-lasting PA changes in the participant. Our intervention study wants to determine the effectiveness of continuous self-monitoring and real-time feedback from the SenseWear Armband alone and in combination with a weekly meeting with a personal coach. We hypothesize that the weekly meeting with a coach will help create an autonomous supportive environment and stimulate the feeling of relatedness. 

## 2. Methods/Design

### 2.1. Study Design

We performed a 12-month randomized controlled trial in which we randomly assigned sedentary male (*n* = 103) and female (*n* = 124) employees to one of four intervention groups: a minimal intervention group received no feedback during the intervention period (MIG; *n* = 56); a pedometer group received information on their daily step count and received a step diary to write down their daily steps (PG; *n* = 57); a display group got personalized feedback by means of the SWA display and received a diary to write done their additional activities (DG; *n* = 57); a coaching group also received the display and diary and additionally had weekly meetings with a coach to discuss the progress they had made (CoachG; *n* = 57). During those meetings, the coach attempted to create an autonomy-supportive environment by encouraging choice and initiation (“how would you increase your activities this week?”), providing participants with different options (“maybe you could go for a walk during your lunch break or travel to work by bike?”), giving informational positive feedback, and acknowledging that the feeling of competence grows from feedback inherent to task (“well done, this week you participated at least more than one hour a day in PA”).

Outcome measures were assessed during a baseline assessment and again at 3, 6, and 12 months. The primary outcome of the study is the level of physical activity (PAL). Secondary outcome measures include step count, minutes of physical (in)activity (sedentary, light, moderate, vigorous, and very vigorous intensity PA), daily energy expenditure in PA, percentage of participants losing fat percentage, and stages of motivational readiness for PA.

### 2.2. Description and Selection Criteria of Participants

All participants were recruited from working places in Flanders (Belgium) through flyers, emails, pharmacists, and word of mouth. Employees (male and female) aged between 19 and 67 years who mentioned not being physically active during the last year, who are interested in knowing how many calories they burn in daily life, and who are motivated wearing the SenseWear Armband during 6 weeks were recruited. 

### 2.3. Participant Screening

Participants' flow of the study is shown in Figure 1. All study participants progressed through the study, beginning with an initial contact in which participants are invited to go to an information session. At this session, potential participants received an explanation regarding the purpose of the study and study expectations. This discussion included the participant responsibilities and potential health benefits and risks related to study participation. All interested participants had to sign an informed consent approved by the Medical Ethics Committee of the KU Leuven and were scheduled to take part in a baseline measurement. During baseline measurement, participants completed standardized measurements including height, weight, resting blood pressure, resting heart rate, waist and hip circumference, and measurement of fat percentage. Participants received the armband with oral and written instructions for proper wear and were given the opportunity to wear and adjust the armband. They were asked to wear the armband for 7 days to assess baseline physical activity level (bPAL). Participants received no feedback from the armband during this period. Participants were asked to fill in the Flemish Physical Activity Computerized Questionnaire (FPACQ; [45]) about their self-reported physical (in)activity pattern and were asked to complete some other questionnaires regarding their medical history, sports and activity history, and job status. The armband and the questionnaires were returned during their next visit. Previous research showed that both Saturday and Sunday and at least 3 weekdays needed to be monitored to obtain reliable measures of habitual physical (in)activity [46]. Only participants with a bPAL value lower than 1.71, wearing the armband for more than 95% of the time and had at least 3 days of monitoring from Monday through Friday and both Saturday and Sunday measured, were eligible to continue. 

### 2.4. Randomization

After successfully completing the baseline measurement and signing the informed consent, eligible participants were randomized into one of the four groups. During the randomization visit, all participants received an evaluation of their baseline measurement. The feedback report also gave information about the benefits of an active lifestyle, the current PA recommendations, how to get active in daily life, and tips for starting PA.

Table 1 shows the descriptive statistics of our study population. Our population includes participants with a bPAL ≥ 1.71 MET (Act), individuals that dropped out from the intervention trial (DO), and the four intervention arms (MIG, PG, DG, and CoachG). The randomization process achieves a reasonable balance across the four intervention arms at baseline. After exclusion of the active group and the drop-out group, post hoc tests reveal a difference in bPAL between the PG and DG of 0.08 MET for the total group and 0.11 MET for the male group. No difference in bPAL exists between the PG and DG for the female group. 

### 2.5. Followup Examinations

Followup data collection visits occurred at 3, 6, and 12 months after randomization and was collected between October 2010 and July 2012. The same measurements completed during the baseline session were assessed during each followup visit. Participants were also asked to fill in the FPACQ to assess detailed information on several dimensions of PA and sedentary behavior over a usual week. After each followup measurement, participants received feedback about their physical (in)activity level and a comparison was made with previous measurements.

### 2.6. Outcome Measurements and Methods

The Primary outcome measurement is the physical activity level (PAL). Secondary outcome measures include step count, minutes of physical (in)activity (sedentary, light, moderate, vigorous, and very vigorous intensity PA), daily energy expenditure in PA, percent of participants losing fat percentage, and stages of motivational readiness for PA. 

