#### 2.6.1. Anthropometric and Physiological Measures

During each assessment, several measures were obtained including height, weight, hip, and waist circumference, resting blood pressure, resting heart rate, and fat percentage. Resting heart rate and resting blood pressure were measured alternately three times to improve measurement accuracy. Height and weight were assessed without shoes using a portable stadiometer of Martin (GPM anthropological instruments, Zurich, Switzerland) and a digital scale (Seca, Hamburg, Germany). BMI is calculated as body weight/height². The same measuring tape with tension rod was used for each waist and hip circumference measure. The waist was measured at the smallest circumference of the natural waist, just above the belly button. Hip circumference was assessed with the measuring tape being placed just above both iliac crests. Bioelectrical impedance analysis (BIA) was used to obtain a complete analysis of the body composition (percent distribution of body fat). All participants were measured by the same person.

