### 2.7. Statistical Analysis

Differences between the four study arms in PA outcomes will be tested according to the intention-to-treat philosophy. All participants' data will be analyzed according to their group assignment at randomization, regardless of adherence to the intervention. The PA outcomes being studied are daily energy expenditure (DEE), active energy expenditure (AEE), minutes of PA, physical activity level (PAL), and steps. A primary comparison is between the PA outcomes of groups who receive feedback (step group, display group and coaching group) and the group receiving no feedback (minimal intervention group). We hypothesize that getting feedback on the PA pattern will alter the PAL compared to having no information. Secondly, a comparison will be made on the difference in PA variables between participants who received feedback by means of the SWA display (display group) and participants who are only given information on their daily step count using a simple pedometer (step group). Since the SWA display gives more detailed information on different PA variables (minutes of PA, DEE, and steps) in contrast to the pedometer which only gives information on the daily step count, it is expected that people from the display group will have more benefits of the intervention compared to those belonging to the step group. Finally, the additional effect of a coach having weekly meetings with the participants will be evaluated. We hypothesize that the power of the interaction of a coach will result in an increase of the PA outcomes compared to subjects only receiving information by means of a technological instrument (display group and step group). Differences in PA outcome measures will be examined using analysis of covariance (ANCOVA) models of 12-month change scores. Self-reported PA, awareness, and cognitions will be analyzed as secondary outcomes. All analyses take into account specified covariates, including age, gender, BMI, education, percentage of armband wearing time, and baseline values of PA outcome measures. 

Based on our results from a pilot study (*n* = 52; PALpre = 1.41 ± 0.11 METs), an a priori power analysis was performed to determine the sample size necessary to detect a significant increase in energy expenditure in the intervention groups. Sample size calculations showed that 57 subjects in each group would give 80% power to detect a difference in PAL between baseline and posttest at a significance level of *P* < 0.05.

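### The body-fat secondary outcome counts only whether fat percentage fell, discarding about 36% of the information in a continuous measure (normal changes centred near zero)

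*Protocol article*

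**What the plan says.** Section 2.1 (Study Design) lists among the secondary outcomes the "percentage of participants losing fat percentage", and section 2.6 (Outcome Measurements and Methods) repeats it as "percent of participants losing fat percentage". Neither section gives a minimum loss or names change in percent body fat as an outcome.

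Section 2.6.1 describes the measurement: "Bioelectrical impedance analysis (BIA) was used to obtain a complete analysis of the body composition (percent distribution of body fat"). For heart rate and blood pressure it adds that "Resting heart rate and resting blood pressure were measured alternately three times to improve measurement accuracy"; it mentions no repeat readings for bioimpedance. Section 2.5 states that "The same measurements completed during the baseline session were assessed during each followup visit", so a continuous value exists at baseline, 3, 6 and 12 months. Table 1 reports percent body fat as mean (SD), with means of 28.4 to 29.6 and SDs of 5.8 to 6.9 across the four arms.

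Section 2.7 plans a continuous analysis for the activity outcomes: "Differences in PA outcome measures will be examined using analysis of covariance (ANCOVA) models of 12-month change scores". Body fat is not among the outcomes it lists there.

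**The concern.** A yes/no outcome cut at no change has two weaknesses.

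- **It is hard to interpret.** A stable participant measured twice with symmetric error shows a fall about half the time. An arm in which half the participants lost fat may therefore be an arm in which nothing happened. A very small fall also counts the same as a large one.
- **It is inefficient.** The size of each change is measured and then discarded, so a given true difference between arms is harder to detect.

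At stake is the trial's only listed body-composition outcome. The primary outcome, PAL, is not touched.

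**Working it through.** **Inputs from the protocol article.** Arm sizes are 56 (minimal intervention) and 57 in each of the other three, so the three feedback arms together have 57 + 57 + 57 = 171. Section 2.7 uses a 0.05 significance level. I take tests as two-sided, which is an assumption.

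**Not in the article.** It gives no SD of change in percent body fat, no bioimpedance error and no target difference for body fat. Effect sizes below are therefore in SDs of change and are illustrative.

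**The plan's own figure.** The only sample-size statement is that "57 subjects in each group would give 80% power to detect a difference in PAL between baseline and posttest". It gives no target difference, so it can be neither confirmed nor refuted. Read as a two-arm comparison, 57 per arm with 80% power corresponds to (1.960 + 0.842) × √(2/57) = 0.525 SD. That is where the illustrative effect of about 0.53 SD comes from. The article claims no power for body fat.

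**Step 1: chance of counting as a loss with no true change.** With continuous readings and symmetric error, the probability is 0.50. Rounding to 0.1 point creates some ties. In a simulation with an assumed error SD of 0.5 to 2.0 points per reading, the share showing a fall is 47% to 49%.

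**Step 2: information kept.** Let the change be normal, with c the mean fat loss divided by the SD of change, and p = Φ(c) the proportion losing fat. The efficiency of the yes/no outcome relative to the mean change is φ(c)² / [p(1 − p)].

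| c | p | Efficiency | Loss |
|---|---|---|---|
| 0 | 0.500 | 2/π = 0.637 | 36% |
| 0.25 | 0.599 | 0.622 | 38% |
| 0.50 | 0.691 | 0.581 | 42% |
| 1.00 | 0.841 | 0.439 | 56% |

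Under normality, 36% is the smallest loss. Adjusting the continuous outcome for its baseline widens the gap: at c = 0 the efficiency becomes (2/π)(1 + r)/2, where r is the correlation between baseline and follow-up. For an assumed r of 0.5 to 0.95 this is 0.477 to 0.621, a loss of 52% to 38%.

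**Step 3: power, 57 v 57, effect 0.526 SD, comparison-arm mean change 0.**

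- Continuous: SE = √(2/57) = 0.187; power = Φ(0.526/0.187 − 1.960) = 0.80.
- Yes/no: p₁ = 0.500, p₂ = Φ(0.526) = 0.701. The SE is 0.0918 under the null (pooled) and 0.0898 under the alternative; power = Φ[(0.2006 − 1.960 × 0.0918)/0.0898] = Φ(0.23) = 0.59.
- The yes/no outcome needs 93 per arm for 80% power, against 57.

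**Step 4: power, 56 v 171, effect 0.40 SD, same setting.**

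- Continuous: SE = √(1/56 + 1/171) = 0.154; power = Φ(0.40/0.154 − 1.960) = 0.74.
- Yes/no: p₁ = 0.500, p₂ = Φ(0.40) = 0.655, pooled p = 0.617. The SEs are 0.0748 and 0.0761; power = Φ[(0.1554 − 1.960 × 0.0748)/0.0761] = Φ(0.11) = 0.55.

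A simulation of 40,000 replicates, comparing a t-test on the change with a two-proportion test of any fall, gives the same pairs: 0.80 v 0.59 (at 0.53 SD) and 0.74 v 0.55.

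**The case against.** The best defence is that this is one item in an open-ended list of secondary outcomes, that a responder percentage is a familiar summary, and that an article may leave an operational threshold to the full protocol. The list does not forbid reporting mean change as well. All of this bears on how serious the point is. It does not remove it: the outcome is worded the same way in two sections, no threshold appears in either, and no continuous body-fat outcome is named.

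The efficiency figure is also conditional. It needs roughly normal changes; with heavy tails the loss shrinks and can reverse. The effects of 0.53 and 0.40 SD are not the article's.

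Two stronger readings are tempting, and the document supports neither.

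- A reader might infer that the yes/no outcome clashes with the planned ANCOVA. Section 2.7 confines that model to the activity outcomes: "The PA outcomes being studied are daily energy expenditure (DEE), active energy expenditure (AEE), minutes of PA, physical activity level (PAL), and steps". Nothing says body fat will go through it, and a binary model could also adjust for baseline fat.
- A reader might infer that the reported percentage will be mostly noise. That depends on how true change compares with measurement error, and neither bioimpedance error nor the SD of change is given. The 50% figure applies only to a person with no true change.

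**Conclusion.** The point holds as an avoidable weakness in a secondary outcome. Taken as any decrease, the definition lets a person with no true change count as losing fat about half the time. It keeps about 64% of the information if changes are near normal and centred near zero, and less if average change under normality is away from zero. In the assumed scenarios that means a fall in power of 21 percentage points (80% to 59%) or 19 (74% to 55%). Error that is the same in all arms dilutes the contrast without favouring any arm, so the cost is power and interpretability, not bias towards an intervention. No stated figure in the article is wrong on this account, and neither the PAL analysis nor the sample size depends on it.

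**What to change.** Make the tested body-fat outcome the 12-month change in percent body fat, in percentage points, compared between arms with adjustment for baseline percent body fat and the covariates already listed in section 2.7 (age, gender, BMI, education and armband wearing time). Keep the declared percentage losing fat beside it as a descriptive figure, and state that it means any decrease.

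No new data are needed, only one more model. The real cost is disclosure. Section 2.5 places follow-up between October 2010 and July 2012 and describes it in the past tense, so collection was under way or complete. The report should therefore say that a declared secondary outcome was changed, when and why, and still show the percentage as declared.
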